### Intervention

Stroke patients in all groups will require multidisciplinary medication and rehabilitation; hence, their routine treatment programmes will continue as usual with the additional 4-week intervention. The intervention will be delivered at the same frequency and duration in the three groups: 45 min daily, 5 days/week for 4 weeks. The same therapists and therapy assistants will deliver all the intervention sessions at each centre [12].

Participants in the CT group (conventional therapy) will receive the therapist-mediated arm intervention using conventional therapy techniques, such as muscle strengthening, stretching, arm exercises or gross-motor training, fine-motor training and functional task practice. This therapy matches that in the other groups with respect to schedule and the form and intensity of movements. The programmes in the conventional group will progress to meet the patient’s training goals.

The EXO group (exoskeleton therapy) will receive intensive task-specific training in the three-dimensional workspace of the human arm involving shoulder (flexion/extension, horizontal abduction/adduction, external/internal rotation) and elbow (flexion/extension, pronation/supination) movements (Armule®, Intelbot Intelligent Machine Co., Ltd., Wuhan, China). Each training session consists of exercises in the following order: 5-min passive mode plus 15-min assist-as-needed mode for twice with a 5-min break between intervals. In the passive mode, the exoskeleton manipulates the upper limb in a three-dimensional trajectory predetermined by the therapists according to the patient’s goals. In the assist-as-needed mode, the patients practice games and ADL training programmes dedicated to shoulder and elbow movements. When the patient is unable to complete the tasks actively, assistive force will supply the upper extremity with passive movement to the target positions.

The AOT-EXO group (action observation treatment-based exoskeleton therapy) will share a training routine with the EXO group. The difference is as follows: during the assist-as-needed session in the AOT-EXO group, patients will be instructed to carefully watch video clips showing upper limb movements and related daily routine tasks before training. Each session will last approximately 15 min (2-min action observation and 3-min action execution for three movement sequences) twice per day (upper limb movements followed by related daily routine tasks in the second session). The actors in the videos will be healthy volunteers. The video clips will be obtained with a Canon camera in the first-person perspective [23]. Patients will be presented with three movement sequences per week for 4 weeks with increasing difficulty (12 sequences in total).

### Outcomes

All outcomes will be measured at baseline, post-intervention (at 4 weeks) and follow-up (at 12 weeks) with no charge. The primary outcome will be mean change in the Fugl-Meyer Assessment for Upper Extremity (FMA-UE) score. This assessment examines arm movement, coordination and reflexes, and the results are represented as a 3-point ordinal scale score with a maximum of 66 points. The FMA-UE is a reliable and valid scale with which to measure upper limb motor impairment after stroke, with higher scores indicating better motor function [24].

Secondary outcomes will be the mean change in Action Research Arm Test (ARAT) score, modified Barthel Index (MBI), kinematic metrics, resting motor threshold (rMT) and motor evoked potentials (MEP), functional magnetic resonance imaging (fMRI) and safety outcomes.

The Action Research Arm Test (ARAT) evaluates 19 tests of arm motor function, including four subscales: grasp, grip, pinch and gross movement. Each test is given an ordinal score of 0, 1, 2 or 3, with the total score ranging from 0 to 57, with higher values indicating better arm motor status and dexterity [25].

The modified Barthel Index (MBI) is an assessment tool formulated to examine the level of independence in the basic ADL and comprises 10 categories: feeding, personal hygiene, toilet use, bladder control, bowel control, bathing, dressing, chair/bed transfer, ambulation, and stair climbing [26].

We will use kinematic metrics (Inertial Measurement Unit, IMU, Noraxon USA Inc.) to evaluate the movement smoothness (peak speed, time to peak speed, number of movement units and path ratio) and performance (pointing time and pointing accuracy) during the finger-to-nose test. The instrumented kinematic assessment can provide good sensitivity for detecting motor performance that is not captured by the clinical scales [27, 28].

Corticospinal excitability will be measured using resting motor threshold (rMT) and motor evoked potentials (MEP) from the abductor pollicis brevis (APB) muscles [29]. Patients will be instructed to sit in a comfortable chair with their hands resting on their lap during the evaluations. Transcranial magnetic stimulation (TMS MagVenture® MagPro R30 Denmark) will be performed using a figure-eight coil placed tangentially in a posterior–anterior plane at a 45° angle from the midline over the hotspot. The rMT is defined for each hemisphere as the minimal stimulator output intensity that elicits MEPs with peak-to-peak amplitudes of at least 50 μV from the contralateral APB muscle in at least five of ten trials. MEPs will be sampled during TMS at 110% rMT and will be kept constant during the following evaluations. The MEP will be recorded as zero if not evocable [30, 31].

Functional magnetic resonance imaging (fMRI) acquisition and pre-processing will be conducted as follows. Scanning will be on the same 3.0 Tesla MR scanner (Discovery LS MR 750; GE Healthcare, Chicago, IL, USA), including acquisition of high-resolution anatomical images, followed by two fMRI series of two hemiplegic-sided motor tasks: finger-to-nose motion (task 1) and finger-to-nose motion sequence observation and execution (task 2). The range of motion for each task is not controlled but rather self-determined. Each series contains 30-s epochs that alternate rest with 0.03-Hz movement. We will acquire functional images using the T2*-weighted gradient echo planer imaging sequence, which measures the blood oxygen level dependence (BOLD) signal. Scanning parameters will include 43 axial 3-mm-thick slices of the whole brain per repetition, 204 volumes/series, TR = 3000 ms and TE = 30 ms, matrix size = 72 × 72 and FOV = 216 × 216 mm^2^. During the fMRI scan, subjects will view a guidance video displayed on the screen. The video will run continuously with a 0.03-Hz movement cycle that is green during rest epochs, yellow during task 1 epochs and red during task 2 epochs. For all conditions, each series will consist of 5 cycles alternating between a 30-s baseline block (fixation cross) followed by a 30-s task block, yielding a total duration of each fMRI run of 10 min. Before entering the scanner, subjects will practice the paradigm and an investigator will observe subject movements during scanning to verify task compliance [32].

Pre-processing of fMRI data will be performed with SPM8 (The Wellcome Department of Imaging Neuroscience, University College, London, UK) running in MATLAB (version 7.9.0.529, R2016b) (The MathWorks, Natick, Massachusetts, USA). For each subject, after motion correction, the anatomical MRI will be co-registered to the mean functional image. The fMRI data pre-processing steps include (1) inter-slice timing correction to the middle slice of a volume for signal coherence, (2) realignment of the motion artefact to the first volume in the entire scanning period, (3) co-registration normalization of spatial transformation to the standardized head domain merged from all subjects’ imaging results (the Montreal Neurological Institute template, called the MNI template) and (4) spatial smoothing with a Gaussian kernel of 4 mm full to half-maximum to elevate the signal-to-noise ratio of functional responses.

Safety outcomes will include the occurrence of all adverse events and serious adverse events in accordance with the guidance of the Clinical Trials Ethics Committee of Huazhong University of Science and Technology. Possible adverse events attributable to the intervention may include shoulder pain, skin abrasion and delayed muscle soreness, which will be observed in detail and documented. Establishing causality between the protocol and adverse events will require judgment. We will rate the relevance degree of all adverse events and the intervention in the AOT-EXO trial with an ordinal score from one to five, with higher values indicating a greater degree of relevance. Although robotic training has been proven safe in the previous studies, serious adverse events may occur related or unrelated to our protocol. We have rehearsed an in-hospital first-aid plan that can be carried out expertly under emergency circumstances and will immediately report to the project investigator together with Ethics Committee, who will determine whether the participant needs to be removed from the study and whether the trial should be adjusted or terminated.

### Sample size

The sample size was calculated by considering the primary outcome measure as the reference: a mean difference of 5 points in the FMA-UE between the AOT-EXO group and CT group and 3 points between the AOT-EXO group and EXO group with a standard deviation of 5.0 [33]. Based on multiple comparisons significance level of 1.67% and a power of 0.8, a sample size of 40 per group will be needed. Assuming that 10% patients loss to follow-up, we will choose a sample size of 44 participants for each group and 132 participants in total. The sample size calculation was performed with PASS 2008 software.

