Action observation therapy (AOT) has been applied as an alternative or complement to another approach to rebuild motor function for stroke rehabilitation and was developed on the neurophysiological basis of the mirror neuron system (MNS) [15, 16]. Action observation therapy consists of action observation followed by action imitation and execution, considering that both processes share the matching cerebral motor network. During AOT, patients are instructed to carefully observe the video sequences, imitate them and then practice those movements and motor tasks. Studies have indicated that action observation would induce neural plasticity by promoting activation of the damaged motor circuits that enhance training effects involved in motor learning after stroke [17–19].

Although there have been extensive articles investigating the application of robotic devices and action observation therapy in upper limb rehabilitation after stroke, they fail to show a superior effect in arm function and ADL compared with conventional therapy. Moreover, according to our knowledge, few studies have examined the combined effects and underlying mechanisms of these two techniques. We hypothesize that action observation treatment coupled with robot-assisted training may enhance motor circuit activation and improve upper extremity motor outcomes. Therefore, in this study, we aim to evaluate the effects of action observation treatment-based exoskeleton (AOT-EXO) treatment for the upper extremity after stroke and to explore the potential kinematic mechanisms assessed by inertial measurement unit (IMU) and neurological mechanisms using functional magnetic resonance imaging (fMRI) and corticospinal excitability metrics.

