### Statistical analyses

All statistical analyses will be performed using SPSS software (version 21.0, IBM Corporation, Chicago, IL). To assess the normal distribution of quantitative data, the Shapiro-Wilk test will be employed (*P* > 0.05). Continuous variables will be presented as the mean (SD) for normal distributions and median for non-normal distributions and categorical variables will be presented as frequencies or percentages. Baseline data between groups will be compared using Student’s t-test for continuous variables and the chi-square or Fisher’s exact tests for categorical variables. A *P* value < 0.05 will be considered indicative of statistical significance. All analyses will be carried out based on the intention-to-treat principle, with missing data calculated using multiple imputation. Within-group differences will be assessed using paired t tests for the normally distributed data and Wilcoxon-signed rank test for the non-parametric equivalent test. When comparing the two patient subgroups at each time point, Student’s *t* test (for continuous data) and Fisher’s exact test (for categorical data) will be implemented. When examining the effect of the randomization procedure over time, two-way repeated measures analysis of variance (ANOVA) will be conducted to examine the time-treatment group interaction, with time as the within-group variable and treatment group as the between-group variable.

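### The stated 40 per group does not give 80% power for the 3-point AOT-EXO vs EXO difference: at the stated 1.67% level it gives about 60%

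*Protocol article*

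**What the plan says.** The Sample size section bases the calculation on two differences in the primary outcome. For AOT-EXO vs CT it assumes 5 points. For the other contrast it assumes "3 points between the AOT-EXO group and EXO group with a standard deviation of 5.0". The conclusion drawn from these is: "Based on multiple comparisons significance level of 1.67% and a power of 0.8, a sample size of 40 per group will be needed". Forty is then raised to 44 per group (132 in total) for 10% loss to follow-up. The 80% is not limited to either difference, and sidedness is not given.

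The Statistical analyses section plans Student's t tests for two-group comparisons of continuous data and a two-way repeated measures ANOVA for the time-by-group interaction. It sets one threshold, P < 0.05, and mentions no adjustment for multiple comparisons. The 1.67% level appears only in the Sample size section.

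The Intervention section says that AOT-EXO follows the same training routine as EXO and differs by the video observation added in the assist-as-needed sessions.

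**The concern.** A single sample size is offered as giving 80% power when two quite different differences, 5 and 3 points, are planned with the same SD. The number needed varies with the inverse square of the difference, so the smaller one needs (5/3)² ≈ 2.8 times as many patients. One figure can serve both only if it is set by the smaller difference, and 40 looked too low for that.

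AOT-EXO vs CT mixes the effect of the robot with that of observation. Only AOT-EXO vs EXO shows what observation adds. If the shortfall falls there, the published power is wrong for the contrast closest to the trial's stated idea that "action observation treatment coupled with robot-assisted training may enhance motor circuit activation and improve upper extremity motor outcomes".

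**Working it through.** **Inputs, all from the Sample size section:** differences of 5 and 3 points; SD 5.0; level 0.0167 (consistent with 0.05/3); power 0.80; 40 evaluable per group. Equal allocation comes from Randomization and blinding. Assumption: two-sided test, since sidedness is not stated; one-sided is checked below.

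**Step 1. Try to reproduce 40 per group (normal approximation).** n = 2(z₁₋α/₂ + z₀.₈₀)² SD²/d², with z = 2.393 and 0.842, so (3.235)² ≈ 10.46.

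- d = 5: 2 × 10.46 × 25/25 = 20.9, so 21 per group.
- d = 3: 2 × 10.46 × 25/9 = 58.1, so 59 per group.

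The exact t test (noncentral t) gives 23 and 60. Neither is 40.

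**Step 2. Power with 40 per group.** The standard error of a difference is 5 × √(2/40) = 1.118. The noncentrality is 5/1.118 = 4.47 for 5 points and 3/1.118 = 2.68 for 3 points. The critical t (78 df, two-sided 1.67%) is 2.446.

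- 5 points: 97.7%.
- 3 points: 59.5% (60.2% with the error variance pooled over three groups, 117 df; 61.4% by normal approximation).
- 3 points with all 44 per group evaluable: 64.6%.

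**Step 3. Other readings of the same inputs.**

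| Reading | n per group for 80% | Power at 40 |
|---|---|---|
| 3 points, one-sided 1.67% | 51 | 69.7% |
| 3 points, two-sided 5% | 45 | 75.5% |
| 3 points, one-sided 5% | 36 | 84.5% |
| 3 points, Tukey at 5% | not computed | 62% |
| Both AOT-EXO contrasts significant, 1.67% | not computed | about 60% |
| Overall F test, means 0/2/5, 1.67% | 27 | 95.6% |
| Overall F test, means 0/2/5, 5% | 21 | 98.4% |

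None gives 40. The only 3-point reading that exceeds 80% power at 40 is a one-sided 5% test, which abandons the stated 1.67%.

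**Step 4. What 40 per group would support.** At two-sided 1.67%, 80% power is reached for a difference of about 3.7 points with SD 5.0, or for 3 points with SD of about 4.07.

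**Step 5. The level in the Statistical analyses section.** At two-sided 0.05 the 3-point power is 75.5% with 40 per group and 79.5% with 44. The stated power is therefore missed at either level in the document.

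**The case against.** Four points can fairly be made for the plan.

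- **The 80% may have been meant for the 5-point contrast only.** The section does not say so, and 23 per group would then suffice. Forty matches neither contrast.
- **Baseline adjustment could close the gap.** With a baseline correlation of 0.5 the need falls to about 44 per group, and with 0.6 to about 38. The document states no correlation and plans t tests and repeated measures ANOVA, so this may explain the figure but does not support it.
- **Some inputs cannot be checked.** Sidedness is unstated, the SD rests on a cited source, and the software procedure is not named. The discrepancy lies between the stated SD and the stated n, wherever the SD came from, and it survives either choice of sidedness. What is shown is that 40 is not reproducible; how it arose is not known.
- **The size of the shortfall depends on the level applied.** This stands. A reader might infer that a true 3-point benefit will be missed about 4 times in 10. That holds only if 1.67% is applied in the analysis. Under the written P < 0.05 the miss rate is about 1 in 4.

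Other stronger readings also go too far. The document names no Bonferroni rule; 1.67% is merely consistent with 0.05/3. The 2-point EXO vs CT difference follows only by subtraction (5 − 3) and is not a stated target, so its low power breaks no promise. Nothing in the document proposes reading a null result as proof of no effect.

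**Conclusion.** The concern holds, confined to the 3-point contrast. On the stated SD and 1.67% level, 40 evaluable per group deliver about 60% power two-sided (about 70% one-sided) instead of 80%; 60 per group would be needed. At the P < 0.05 of the Statistical analyses section the power is about 75%.

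The trial as a whole should not be called underpowered: AOT-EXO vs CT has about 98% power. The conclusion assumes a two-sample comparison with common SD 5.0 and no gain from baseline adjustment, as the document is written.

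**What to change.** **Required.** Restate the Sample size section with the power delivered for each contrast: at two-sided 1.67% and 40 evaluable per group, about 98% for 5 points and about 60% for 3 points, with 80% reached only for about 3.7 points or an SD of about 4.07. State sidedness. Make the significance level in Statistical analyses agree with the 1.67% in Sample size. The cost is rewording and a less favourable published power. No patients are added.

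**Options for the trial team, each a trade-off:**

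- A fixed sequence at two-sided 5%: AOT-EXO vs CT, then AOT-EXO vs EXO, then EXO vs CT. With 40 evaluable per group, power is about 99% for the first step and about 75% for passing the first two. It comes close to 80% (79.5%) only if all 44 per group are evaluable, whereas the plan expects 10% loss (44 × 0.9 = 39.6). It therefore does not restore the stated power under the plan's own assumptions. It also changes the testing rule in a recruiting trial and makes the observation contrast depend on the first test.
- Keep 1.67% and enlarge the trial: 60 evaluable per group, or 60/0.9 = 66.7, so 67 enrolled per group and 201 in total against the planned 132. This alone restores 80% on the stated inputs, at the cost of 69 more patients.

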### Data monitoring and management

The data monitoring committee (DMC), independent from the sponsor and competing interests, will be responsible for data monitoring procedure to ensure the accuracy and completeness of the data reported by researchers. The DMC will conduct the procedure at each centre in cooperation with all investigations from institutional review board or regulatory authority. Each centre will be responsible for quality control of the informed consent, participant recruitment, intervention programme implementation and data management.

The directors of each centre will be responsible for retaining all records with complete confidentiality for 10 years after the completion or termination of the study. Each centre will apply data cleansing, identification and coding and will create an electronic data set for statistical analysis and transfer of quality control records. In cases where inconsistencies, missing values or other problems are detected in the data set, the directors at each centre will be queried and will recheck the electronic case report form (CRF) if necessary. The principal investigator and all directors of each centre will receive full anonymous copies of the electronic data set to promote dissemination of the study results.

The sponsor will appoint the Trial Steering Committee (TSC) comprising investigators and clinical experts independent of the clinical trial. TSC will be responsible for the scientific integrity of the clinical trial, including the scientific validity of the study protocol, assessment of study quality and conduct and scientific quality of the final study report.

### Statistical analyses

All statistical analyses will be performed using SPSS software (version 21.0, IBM Corporation, Chicago, IL). To assess the normal distribution of quantitative data, the Shapiro-Wilk test will be employed (*P* > 0.05). Continuous variables will be presented as the mean (SD) for normal distributions and median for non-normal distributions and categorical variables will be presented as frequencies or percentages. Baseline data between groups will be compared using Student’s t-test for continuous variables and the chi-square or Fisher’s exact tests for categorical variables. A *P* value < 0.05 will be considered indicative of statistical significance. All analyses will be carried out based on the intention-to-treat principle, with missing data calculated using multiple imputation. Within-group differences will be assessed using paired t tests for the normally distributed data and Wilcoxon-signed rank test for the non-parametric equivalent test. When comparing the two patient subgroups at each time point, Student’s *t* test (for continuous data) and Fisher’s exact test (for categorical data) will be implemented. When examining the effect of the randomization procedure over time, two-way repeated measures analysis of variance (ANOVA) will be conducted to examine the time-treatment group interaction, with time as the within-group variable and treatment group as the between-group variable.

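### The pairwise FMA-UE comparisons are sized at 1.67% each, but the analysis section gives only P < 0.05 and refers to two groups in a three-arm trial, so the two sections must be reconciled

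*Protocol article*

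**What the plan says.** **Sample size section.** The calculation is described as "Based on multiple comparisons significance level of 1.67% and a power of 0.8". The assumed advantage of AOT-EXO over CT is 5 FMA-UE points. For the second contrast the section assumes "3 points between the AOT-EXO group and EXO group with a standard deviation of 5.0". The result is that "a sample size of 40 per group will be needed", raised to 44 per group for 10% loss. Sidedness is not stated.

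**Statistical analyses section.** After the baseline comparisons comes the section's only significance threshold: a P "value < 0.05 will be considered indicative of statistical significance". Between-group testing is introduced with "When comparing the two patient subgroups at each time point", using Student's t test for continuous data. A two-way repeated-measures ANOVA is then listed to examine the interaction of time and treatment group. The section gives no order of testing, no adjustment and no condition linking the ANOVA to the t tests.

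**Elsewhere.** Study design and Randomization describe three equal groups. Outcomes defines the primary outcome as mean change in FMA-UE, with visits at 4 and 12 weeks after baseline, and does not say which visit is primary.

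**The concern.** The sponsor recognised the multiplicity of a three-arm comparison when sizing the trial, but the decision rule in the analysis section does not reflect it. The two sections give different thresholds for the same primary comparisons.

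This can change the trial's conclusion. With SD 5.0 and 40 completers per group, the smallest significant difference is about 2.2 points at 5% and about 2.7 points at 1.67%. A result between these values is positive or not depending on which section is followed. The contrast most exposed is AOT-EXO against EXO, which isolates the contribution of action observation and was assumed to be only 3 points.

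The reference to two subgroups adds to the problem. With three arms there are three possible pairs, and the section does not say which are to be tested.

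**Working it through.** **Inputs.** From the article: three groups at 1:1:1; 40 per group before loss and 44 after; SD 5.0; differences of 5 and 3 points; levels of 1.67% and 5%; two post-baseline visits. Assumed, because the article does not say: two-sided tests, and a correlation between the 4- and 12-week changes of 0.5 to 0.9.

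**1. The sizing level.** 0.05/3 = 0.0167. This reproduces the stated 1.67% and is the Bonferroni level for three pairwise comparisons.

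**2. Family-wise error, three pairs, one visit.** With a pooled variance and 44 per group, df = 3 × 43 = 129. Under the global null, the chance that at least one pair is significant is the upper tail of the studentized range for three means at √2 × t.

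- At 5%: t = 1.979, √2 × t = 2.798, tail = 12.2%.
- At 1.67%: t = 2.425, √2 × t = 3.429, tail = 4.4%.

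Simulation with separate two-sample t tests (three groups of 44, 60,000 runs) gives the same: 12.2% and 4.4%.

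**3. Other readings, all at 5% per test** (same simulation).

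| Tests that count | Family-wise error |
|---|---|
| The two contrasts named in the sizing, one visit | 9.1% |
| Three pairs, one visit | 12.2% |
| Three pairs, two visits, correlation 0.9 | 16.9% |
| Three pairs, two visits, correlation 0.8 | 18.4% |
| Three pairs, two visits, correlation 0.7 | 19.6% |
| Three pairs, two visits, correlation 0.5 | 20.9% |

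**4. Does 1.67% alone restore 5%?** At one visit, yes (4.4%). If both visits count, three pairs at 1.67% give 6.4% (correlation 0.9) to 8.1% (0.5). A fixed sequence at 5% has the same weakness: its first step, if it may be passed at either visit, has an error of about 7% to 9% over the same correlations. One primary visit has to be named in either case.

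**5. Where the two thresholds disagree.** The critical difference is t × 5 × √(2/40), with df = 78.

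- At 5%: 1.991 × 1.118 = 2.23 points.
- At 1.67%: 2.446 × 1.118 = 2.73 points.

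**6. Power for the 3-point contrast.** The noncentrality is (3/5) × √(n/2), which is 2.68 for n = 40 and 2.81 for n = 44. The noncentral t distribution gives:

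| n per group | Two-sided 1.67% | Two-sided 5% |
|---|---|---|
| 40 | 59.5% | 75.5% |
| 44 | 64.6% | 79.5% |

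With n = 40 and a true difference of 3 points, the result falls between the two thresholds with probability 75.5% − 59.5% = 16%.

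**7. The stated 40 per group.** By the normal approximation, n = 2 × (2.393 + 0.842)² × 25/9 = 58.1, so 59 per group (60 by noncentral t) for 3 points at two-sided 1.67% and 80% power. A one-sided reading gives 49 (51 by noncentral t). The 5-point contrast needs 21 (23 by noncentral t). The stated 40 is therefore more than enough for the 5-point contrast and too few for the 3-point one at the stated level.

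**The case against.** **The article does have a multiplicity level.** The P < 0.05 sentence is a general convention placed straight after the baseline comparisons, and it does not mention the primary outcome. One could read 5% as the overall level and 1.67% as the level for each comparison. That reading is plausible, and it rules out saying that the article ignores multiplicity. It does not remove the conflict: 5% is the only threshold in the analysis section, it is unrestricted, and nothing there points back to 1.67%.

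**There is a three-group test.** The time-by-group interaction in the repeated-measures ANOVA is an omnibus test, so a reader should not infer that the plan consists of two-group tests only. If the pairwise tests were run only after a significant three-group test, the error would stay near 5%: a one-way omnibus gate at one visit with 44 per group gives 5.1% under the global null. This makes the 12% conditional on ungated tests. The article states no such gate and lists the two analyses side by side.

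**A statistical analysis plan may settle this.** Detail can be left to that document. Here, though, the article itself states two levels, and a later plan would have to depart from one of them. This is a contradiction, not an omission.

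**Conclusion.** The concern holds as a conflict between two sections: a design level of 1.67% per comparison that is not carried into an analysis section stating only 5%, together with two-group wording that does not fit three arms.

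The firm figure is a family-wise error of about 12% for three ungated pairwise tests at 5% at one visit, against 4.4% at 1.67%. It is about 9% if only the two contrasts named in the sizing are tested.

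A reader might infer that the primary family-wise error simply is 18%, or some other figure above 12%. The documents do not support stating that as fact. The range of 17% to 21% requires both visits to count as primary, and it depends on a between-visit correlation that the article does not give.

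**What to change.** In the Statistical analyses section, or in a statistical analysis plan that expressly supersedes it:

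1. Name one primary visit for FMA-UE change.
2. Replace the reference to two subgroups with the named pairwise contrasts among the three arms.
3. Test those contrasts at the 1.67% used for sizing. A pre-specified fixed sequence at two-sided 5% at the one primary visit is an acceptable alternative, but the Sample size section must then be restated to match.
4. State whether the ANOVA interaction is supportive or gates the pairwise tests.
5. Label P < 0.05 on all other outcomes as nominal.

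**Cost.** The edits are wording only and can be made before the data are analysed; 12 patients had been enrolled at submission. Fewer results will qualify as significant. The change also exposes a power shortfall: at two-sided 1.67% the AOT-EXO against EXO contrast has about 59% power with 40 per arm and 65% with 44. At 5%, once the sequence reaches that contrast, the figures are about 75% and 79%. The stated 80% should be restated under whichever rule is chosen.
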